## Results

The study (ref: 2020/00810) has been approved by the Domain Specific Review Board of the National Healthcare Group, Singapore. This study is funded by the Biomedical Research Council (BMRC) Singapore COVID-19 Research Fund (Project: 12Al04lg1lA04). All study-related materials, tests, stimuli, and procedures are covered by this funding. Recruitment of participants began on July 23, 2020, and will continue through to March 31, 2021. As of October 2, 2020, 69 participants had been recruited into the study.

## Discussion

### Study Overview

This study will longitudinally track the onset, severity, and recovery of changes in chemosensory (smell and taste) acuity among people with and without COVID-19 infection (following swab testing) using standardized assessment tools that can be used in a residential setting. The objectives of this study are to confirm the association between sudden changes in smell and taste sensitivity and COVID-19 infection in an at-risk population in Singapore; to establish the temporal onset, severity, and recovery of changes in smell and taste sensitivity with COVID-19 infection; to evaluate the efficacy of the SSTT as an early diagnostic tool; and to investigate the effects of loss of smell and taste acuity on appetite and food-related quality of life.

Using a longitudinal prospective study design, we aim to establish the association of the onset, severity, and recovery of smell and taste changes with COVID-19 infection while also providing an initial validation of a rapid, cost-effective, self-administered, and standardized approach to tracking spontaneous changes to taste and smell sensitivity in both clinical and residential settings. These findings will enable better identification of asymptomatic or pre-symptomatic carriers of COVID-19 infection, encouraging earlier self-isolation and medical consultation. Currently, a small number of studies have objectively tested smell and taste acuity in patients with COVID-19, with the majority of studies relying on subjective self-report measures [29]. Given that one-time self-report measures may underestimate the prevalence of olfactory impairment [36,37] and fail to capture temporal changes in sensory acuity, the COVISMIA-19 study provides an objective measurement of smell and taste loss in a sample of patients with COVID-19 that can encourage earlier self-isolation and medical consultation. Furthermore, current household item tests of smell and taste acuity are often not standardized and are heavily reliant on stimuli availability and volunteer compliance [32,33]. The COVOSMIA-19 approach will provide a short, easy-to-use, self-administered test approach that standardizes the smell and taste stimuli and can be easily completed by participants in their own home.

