## Methods

### Study Design

The study will track changes in smell and taste with COVID-19 infection using a prospective longitudinal, case-control study design. Participants will be recruited from volunteers presenting at hospitals and hospital facilities across Singapore for COVID-19 screening. After providing informed consent, the study participants will be asked to report on changes in their smell and taste sensitivity in the previous 2 weeks via a series of questionnaires; they will also be asked to prospectively track daily changes in smell and taste acuity using a self-assessment test and a series of questionnaire measures to measure the onset, severity, and recovery of changes in their chemosensory acuity for the next 28 days. A schematic of the study procedure is shown in Figure 1, and the schedule for enrolment and assessment is shown in Table 1.

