**Assessments**								
	Baseline variables: gender, age, education status, nationality, ethnicity, employment status, smoking status, vaping status, medication, COVID-19 test result		✓					
	Primary outcome variables: COVID-19 symptoms (and onset), smell and taste acuity			✓	✓	✓	✓	✓
	Secondary outcome variables: appetite, food enjoyment, eating behaviors, nausea, weight, food-related quality of life		✓	✓	✓	✓	✓	✓

^a^SSTT: Singapore Smell and Taste Test.

^b^Participants were asked to complete the SSTT daily from Day 1 to Day 28.

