### Recruitment Procedure

Participants will be recruited from patients applying to a hospital and its ancillary units for COVID-19 screening by nasal swab polymerase chain rection (PCR) testing. Following their COVID-19 screening, individuals will be approached and invited to participate in this study and to provide informed consent.

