### Measures

On the day of their COVID-19 swab test (Day 0), after consenting to participate in the trial, participants will complete three questionnaires to document recent changes in their smell, taste, and chemesthetic ability and to detail the frequency of a wide range of nasopharyngeal symptoms. These questionnaires include the Singapore Smell and Taste Questionnaire (SSTQ, Multimedia Appendix 1), the 22-item Sino-Nasal Outcome Test (SNOT-22) [34], and the recently developed Global Consortium for Chemosensory Research questionnaire (GCCRQ) [12]. Participants will receive the Singapore Smell and Taste Test (SSTT, Multimedia Appendix 2), a standardized home use testing kit to monitor their smell and taste acuity, and will be given a demonstration of the self-assessment procedure that they will complete daily at their place of residence for the following 28 days. All the questionnaires and instructions are available in English, Mandarin, Tamil, and Bengali, and the participants will complete all the measures via Compusense Cloud web-based data acquisition software (Compusense Inc).

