### Statistical Analysis

Using a case-control study design for people testing positive (case) or negative (control) for COVID-19 infection, data will be collected on changes in smell and taste loss that have occurred in the 2 weeks prior to the COVID-19 test and on smell and taste acuity changes measured on a daily basis for up to 28 days following the COVID-19 test. The data will be used for descriptive comparisons of the onset, duration, and severity of smell and taste changes with COVID-19 infection and to report on the incidence of these changes among participants testing positive for COVID-19 infection (and those recovering from infection).

Logistic regression analysis will be used to estimate the odds ratio for loss of smell and taste sensitivity as a predictor of testing positive for COVID-19 infection. This will also enable comparison of smell and taste loss as a predictor of COVID-19 infection compared to other symptoms, such as fever and dry cough. Pearson correlations will be used to investigate relationships between smell and taste changes and other symptoms. Time-series analysis of variance (ANOVA) models will be run to investigate temporal changes in smell and taste ratings over time, with baseline ratings in smell and taste acuity corrected for at an individual level. Linear mixed models will be used to test for significant differences in smell and taste acuity between groups, with participants stratified by their COVID-19 infection status.

Factor analyses, using oblique rotation and baseline home-use test responses (conducted in-clinic), will be conducted to assess the internal consistency of our smell and taste test. Adjusted odds ratios will be calculated to investigate the best predictors of recovery of smell and taste acuity postinfection. Linear regression will be run to examine whether responses to the smell and taste test predict responses to the household item odor test (smell) and self-reported taste acuity, respectively. Regression analyses will be conducted to investigate the association between loss of smell and taste acuity and self-reported appetite and food-related quality of life. All statistical analyses will be completed using SPSS (IBM Corporation).

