### Study Strengths

A strength of the COVOSMIA-19 study is the longitudinal nature of the participant surveillance and the parallel application of both the questionnaire self-report and standardized test measures for the assessment of loss of smell and taste acuity. Objective measurements of smell and taste acuity are likely to be more reliable [38] and have not yet been used to longitudinally assess smell and taste changes associated with COVID-19 infection. Standardized test stimuli for the home-use test (SSTT) are provided, and longitudinal data collection will be completed remotely via a web-based platform to encourage adherence and facilitate completion of the procedures by the participants in their own home. All test stimuli have been pretested to ensure standardized concentration and stimuli stability and can be used by individuals regularly throughout a period of self-isolation. This approach will both standardize measurement for improved comparison longitudinally and reduce the risk of cross-contamination associated with sharing test measures or attending laboratory testing.

This study will provide new knowledge to increase our understanding of smell and taste losses associated with COVID-19 infection and will evaluate a simple test procedure for future tracking of these changes among individuals with suspected COVID-19 infection form their own home. Through this study, we aim to better identify individuals who suspect COVID-19 infection but are otherwise asymptomatic or have very mild symptoms, encouraging earlier self-isolation and medical consultation.

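### Every SSTT falls on or after the swab day in people already presenting for testing, so the design cannot show early detection, and the planned regression does not isolate participants without other symptoms

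*Protocol article*

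**What the plan says.** **Claims.** Study Overview lists among the objectives "to evaluate the efficacy of the SSTT as an early diagnostic tool" and then asserts: "These findings will enable better identification of asymptomatic or pre-symptomatic carriers of COVID-19 infection, encouraging earlier self-isolation and medical consultation". Study Strengths says that through the study "we aim to better identify individuals who suspect COVID-19 infection but are otherwise asymptomatic or have very mild symptoms". The conclusions of the Abstract likewise expect the approach to prompt people without other symptoms to isolate and seek diagnosis.

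Two other sections describe the SSTT aim without the word *early*. The Introduction frames it as a rapid, inexpensive measure to be compared with household-item tests. Primary Outcomes calls it a simple diagnostic approach.

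**Design.** Study Design gives the source population: "Participants will be recruited from volunteers presenting at hospitals and hospital facilities across Singapore for COVID-19 screening". Recruitment Procedure gives the order of events: "Following their COVID-19 screening, individuals will be approached and invited to participate in this study and to provide informed consent". Measures fixes Day 0: "On the day of their COVID-19 swab test (Day 0), after consenting to participate in the trial, participants will complete three questionnaires". Table 1 places the initial SSTT session in clinic on Day 0, and its footnote covers the rest: "Participants were asked to complete the SSTT daily from Day 1 to Day 28".

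**Analysis.** Statistical Analysis states: "Logistic regression analysis will be used to estimate the odds ratio for loss of smell and taste sensitivity as a predictor of testing positive". The same model is to compare smell and taste loss with symptoms such as fever and dry cough.

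**The concern.** A test can be shown to be early only if it is applied before the event it is meant to anticipate, or to people who have not yet reached that point. Here the event is the diagnostic swab, and everyone enrolled has already had it. The Introduction faults existing work for not following people from before infection and for relying on self-report. Yet the only pre-swab information in this study is recalled self-report.

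At stake is a public-health statement about finding people who spread infection without knowing it. If the regression is positive, the Discussion as worded would carry that result over to early detection and to carriers without symptoms. The result itself would be a concurrent association, on the day of testing, in people who came for a test. An odds ratio from that mix need not apply to people with no other symptom.

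**Working it through.** The point rests mainly on timing, so the passages are set side by side. The only arithmetic is a session count, a check of the stated sample size, and an illustration under outside assumptions.

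**1. When the SSTT is done.** One session on Day 0 plus 28 daily sessions makes 1 + 28 = 29. Approach and consent follow the screening, so the Day 0 session comes after the swab on the same day. Sessions before the swab: 0 of 29.

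**2. What it is compared with.** Under COVID-19 Diagnosis, infection status is the outcome of the diagnostic swab, linked afterwards to the participant's identifier. No repeat PCR is described. Daily sessions therefore cannot be matched to a later conversion in someone who was negative on Day 0.

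**3. What covers the period before the swab.** Study Design and Statistical Analysis refer to the preceding 2 weeks, covered by questionnaire. That is recall, with no SSTT behind it.

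**4. Who is tested.** All participants presented for screening. There is no untested comparison group, so whether the SSTT brings people forward sooner is not observed.

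Steps 1 to 4 settle the *early* claim. No statistical analysis plan, seen or unseen, can supply an SSTT result from before the swab.

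**5. Whether people without other symptoms can be studied.** They can. The inclusion and exclusion criteria do not mention symptoms. The SSTQ records symptoms and their onset on Day 0, and each daily session includes a symptom checklist. Data Management already requires the SSTQ, the in-clinic SSTT and the swab result for the cross-sectional comparisons. Swab-positive participants with no other symptom on Day 0, including those who develop symptoms later, can be picked out and set against swab-negative participants with no other symptom.

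**6. What the planned regression estimates.** It estimates one odds ratio for smell and taste loss across everyone enrolled. Setting it beside fever and dry cough ranks predictors in the pooled sample. Without a restriction or an interaction term, it does not estimate how loss discriminates among people who have none of the other symptoms.

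**7. The stated sample size.** Inputs from Sample Size Determination: base probability 0.20, odds ratio 1.723, power 95%, significance level 0.05. With b = ln(1.723) = 0.544, a standard-normal predictor and Demidenko's method with variance correction:

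n = (z_α·√v0 + z_β·√v1)² / b²

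Here v0 and v1 are the per-subject variances of the slope under the null and the alternative. One-sided, this gives 234.6, so the stated 235 is reproduced (two-sided it gives 280). The figure sizes the whole sample. No subgroup is sized.

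**8. Illustration of subgroup size.** The documents give neither the expected positivity nor the share of positives without other symptoms. Purely as assumptions, take positivity of 5% to 30% and a symptom-free share of 20% to 40%:

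- Low end: 235 × 0.05 × 0.20 = 2.35, about 2 swab-positive participants. If 1 of 2 shows loss, the exact 95% interval for sensitivity is about 1% to 99%.
- High end: 235 × 0.30 × 0.40 = 28.2, about 28. If 14 of 28 show loss, the interval is about 31% to 69%.

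Across this assumed range the estimate is imprecise.

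**The case against.** The best reply has four parts.

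*The sentences are Discussion aspirations.* The Introduction and Primary Outcomes do not say *early*, and Study Overview speaks of an initial validation. This is a fair point about emphasis. But the phrase appears in a list of the study's objectives, and the sentence about carriers says what the findings will do. The limitations section covers compliance and the suprathreshold stimuli; it does not mention timing or recruitment from people presenting for testing.

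*Early may mean early in the course of infection.* The Introduction does say that loss often precedes more established symptoms, so this reading is open. On that reading the evidence would have to come from participants with no other symptom on Day 0, or from the order of symptom onset. The first is not isolated in the stated regression. The second is recalled wherever it precedes Day 0.

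*A subgroup analysis may sit in a document not shown.* This stands. The article is condensed and refers to a fuller protocol, so the absent subgroup is the secondary part of the point. The article also plans descriptive comparisons of onset and correlations with other symptoms. The timing argument does not depend on either.

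*A Day 0 SSTT alongside the swab is a normal way to compare an index test with a reference test.* This also stands, and it is why the diagnostic outcome can be kept in restated form.

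**Conclusion.** The point holds as a mismatch between a stated objective and conclusion and what the design can deliver. With 0 of 29 SSTT sessions before the swab, and all participants already presenting for screening, detection ahead of the swab and earlier presentation of untested people cannot be shown. The pooled regression does not support the statement about carriers. This changes what the study may conclude; recruitment, measurement and sample size are unaffected. It rests on the schedule and the single swab result being as the article describes them.

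Three stronger readings are tempting and are not supported:

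- A reader might infer that the study can say nothing about carriers without symptoms. Eligibility and the Day 0 and daily symptom records show otherwise.
- A reader might infer that the cohort is mostly symptomatic. No symptom mix is stated.
- A reader might size the subgroup by applying the 0.20 in the power calculation and the one-in-six isolated-anosmia figure in the Introduction. The 0.20 is a power input under the null, not a forecast of positivity. The other figure, from a cited study, counts patients whose only symptom is smell loss; the analysis needed here also includes positives with no symptom at all, and swab-negative controls. The size of the subgroup cannot be calculated from the documents.

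**What to change.** 1. In Study Overview, delete *early* and align the SSTT objective with the Introduction and Primary Outcomes. State the diagnostic outcome as concurrent discrimination of swab-positive from swab-negative participants on Day 0.
2. Prespecify a Day 0 analysis of loss by SSTT and by SSTQ against swab result, restricted to participants reporting no other COVID-19 symptom on Day 0, and report it with its confidence interval.
3. Among cases, report whether smell or taste loss preceded, coincided with or followed the first other symptom, labelled as recalled where it precedes Day 0.
4. Make the statements about carriers in the Abstract conclusions, Study Overview and Study Strengths conditional on item 2, and limit them to people who present for testing.

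Cost: protocol and analysis wording, and two analyses of data already being collected. No visit, measure or participant is added. The downside is a weaker headline claim and a subgroup estimate that will probably be imprecise.

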### Study Limitations

There is potential for poor compliance by volunteer participants in completing their daily assessments throughout all 28 days of the assessment period. To mitigate this, all questionnaires and home-use test procedures will be short and easy to complete while maintaining the scientific rigor of the test approach. Similarly, the SSTT test measures focus on detecting changes in “usual” sensory perception, and the stimuli have deliberately been selected to monitor changes in suprathreshold perceptual intensity. As such, the SSTT approach will not provide information regarding changes to smell and taste at the perithreshold level (ie, identification, detection discrimination thresholds) or profile odor identification across a wide range of odor stimuli to identify specific anosmias. Although participants will be texted daily reminders to complete their daily home-use tests, their participation is entirely voluntary, with potential for poor adherence and retention. Our proposed procedure for handling potential missing data scenarios are outlined previously (see the Data Management section).

### Study Strengths

A strength of the COVOSMIA-19 study is the longitudinal nature of the participant surveillance and the parallel application of both the questionnaire self-report and standardized test measures for the assessment of loss of smell and taste acuity. Objective measurements of smell and taste acuity are likely to be more reliable [38] and have not yet been used to longitudinally assess smell and taste changes associated with COVID-19 infection. Standardized test stimuli for the home-use test (SSTT) are provided, and longitudinal data collection will be completed remotely via a web-based platform to encourage adherence and facilitate completion of the procedures by the participants in their own home. All test stimuli have been pretested to ensure standardized concentration and stimuli stability and can be used by individuals regularly throughout a period of self-isolation. This approach will both standardize measurement for improved comparison longitudinally and reduce the risk of cross-contamination associated with sharing test measures or attending laboratory testing.

This study will provide new knowledge to increase our understanding of smell and taste losses associated with COVID-19 infection and will evaluate a simple test procedure for future tracking of these changes among individuals with suspected COVID-19 infection form their own home. Through this study, we aim to better identify individuals who suspect COVID-19 infection but are otherwise asymptomatic or have very mild symptoms, encouraging earlier self-isolation and medical consultation.

## Appendix

Multimedia Appendix 1 Singapore Smell and Taste Questionnaire (SSTQ).

Multimedia Appendix 2 Daily smell and taste testing documents.

Multimedia Appendix 3 Table S2. Questionnaire items and their sources.

## Abbreviations

ANOVA: analysis of variance
BMRC: Biomedical Research Council
GCCRQ: Global Consortium for Chemosensory Research questionnaire
PCR: polymerase chain reaction
QR: quick response
SESOI: smallest effect size of interest
SNOT-22: 22-item Sino-Nasal Outcome Test
SSTQ: The Singapore Smell and Taste Questionnaire
SSTT: Singapore Smell and Taste Test
UPSIT: University of Pennsylvania Smell Identification Test
VAS: visual analog scale
